## Abstract

**Background:**

Allergic rhinitis (AR) is a worldwide health problem. Allergen avoidance is strongly recommended for AR patients. Air purification can reduce concentrations of particles in indoor air, including those of allergens. Air purifiers have been recommended by clinicians for AR patients, but few studies have focused on the removal of airborne allergens from home environments. Such studies have been limited by a lack of blinding, small samples, or a failure to measure allergen levels, disease activity, or a combination of these factors. This study investigates the efficacy of a high-efficiency air purifier in reducing disease activity in the homes of AR patients sensitive to the allergens produced by *Artemisia* (mugwort) pollen.

**Methods:**

This is a randomized, double-blind, clinical controlled trial that will test active and inactive versions of an air purifier (Atmosphere®; Amway China). Sixty AR patients sensitive to the allergens produced by *Artemisia* pollen will be assigned randomly to two groups of equal numbers. All patients will undergo a 4-week treatment period and a 4-week observation period. Evaluation will be conducted at baseline (day 0) and on days 7, 14, 21, 28, and 56. The primary outcome measure will be the difference in visual analog scale scores from baseline. Secondary outcomes will be changes from baseline in nasal symptoms, allergy symptom scores, responses to the Rhinoconjunctivitis Quality of Life Questionnaire, Epworth Sleepiness Scale scores, and tolerability scores for the air purifier. Side effects of treatment will be recorded.

**Discussion:**

Reducing exposure to allergens can reduce the risk of conditions such as AR. We hypothesise that AR patients sensitive to the allergens produced by Artemisia pollen will not suffer symptoms in a pollen-free environment. AR patients can remove pollen from their homes using air purifiers, decreasing the risk of symptoms. We expect that our study results will provide reliable evidence for determining the effects of air-purification therapy.

**Trial registration:**

ChiCTR-INR-17012481. (Retrospectively registered 26 August 2017).

## Background

Allergic rhinitis (AR) is a global health problem. The reported incidence of AR is 11.8–46% worldwide [1, 2] and 11.1–19.1% [3, 4] in China. Allergen avoidance is strongly recommended for AR patients. In Japan, a country-wide map of pollen concentrations is published daily so that AR patients can avoid high-concentration areas [5]. Seasonal migration of AR patients is an effective but expensive option. We searched for more convenient and less expensive ways to avoid and mitigate allergen exposure.

Our research team focused on air purification because this strategy can reduce the concentrations of particles in indoor air. In addition, air purifiers can filter particles smaller than 1 μm in diameter [6], and the diameter of mugwort (*Artemisia* spp.) pollen is typically 19–25 μm [7] .Air purifiers are recommended by clinicians for AR patients [8], as they can reduce airborne indoor allergen levels significantly [9]. Few studies, however, have focused on the removal of airborne allergens in home environments. Moreover, those studies have been limited by a lack of blinding, small samples, and a failure to measure allergen levels, disease activity, or a combination of these factors.

### Project aim

Studies have suggested that indoor particle purification may reduce clinical symptoms or improve clinical outcomes, particularly for individuals with allergies [10] .Little robust clinical evidence has been provided, however, for the efficacy of indoor-air purification as a treatment. We sought to investigate, by means of a double-blind, placebo-controlled protocol, the efficacy of a high-efficiency particulate air (HEPA) purifier in reducing disease activity in the homes of AR patients sensitive to the allergens produced by *Artemisia* pollen.

## Methods/Design

### Design

This is a randomised, double-blind, placebo-controlled clinical trial that tests active and inactive versions of an air purifier. The air purifiers are equipped with monitors to measure the number of hours they operate. AR patients sensitive to the allergens produced by *Artemisia* pollen will be assigned randomly to two groups of equal numbers. All patients will accept a 4-week treatment period and a 4-week observation period. Patient evaluation will be undertaken at baseline (day 0) and on days 7, 14, 21, 28, and 56 (Table 1). Figure 1 displays a flowchart of the study design. Specific tests that will be conducted at each follow-up occasion are outlined in Table 1.

**Table 1 Tab1:** Schedule of patient evaluation

Outcome measures	Screening stage	Remedial period				Observation period
	Baseline	Day 7	Day 14	Day 21	Day 28	Day 56
Nasal symptoms	X	X	X	X	X	X
Allergy symptom score	X	X	X	X	X	X
Visual analog scale score	X	X	X	X	X	X
Rhinoconjunctivitis Quality of Life Questionnaire	X	X	X	X	X	X
Epworth Sleepiness Scale score	X	X	X	X	X	X
Tolerability of the air purifier		X	X	X	X	
Treatment compliance		X	X	X	X	
Safety assessment		X	X	X	X	X

**Fig. 1 Fig1:**
[figure not shown]
Flowchart of the study design

### Setting

Study activities will be conducted at different settings. Patient enrollment and specimen and data collection will be conducted in the Outpatient Department of the First Hospital of Yulin (Guangxi, China). Biochemical examinations will be undertaken by King Med Diagnostics (Guangzhou, China). Data analyses will be performed at the University of Toronto (Toronto, ON, Canada).

### Study procedures

#### Staff training

Personnel who participate directly in this study will be trained to ensure the safety of patients, blinding of the study design, and data quality.

#### Sample size

The mean changes in findings before and after treatment were used as the indicator for efficacy evaluation in calculation of the sample size. We defined efficacy as changes in at least one score with the visual analog scale (VAS). Using a ratio of 1:1, α = 0.05, and 1 − β = 0.8 with a one-sided *t*-test, we calculated the appropriate trial sample size with 80% power. We found that a clinically significant difference could be detected using a sample of ≥21 patients in each group. We increased this number to 30 per group to allow for a predicted dropout rate of 30%.

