### Statistical analyses

Statistical analyses will be carried out using SPSS v. 17.0 (IBM, Armonk, NY, USA) in the Clinical Evaluation Center of Southern Medical University (Guangzhou, China). Data will be described as the mean and standard deviation for normally distributed data, median and interquartile range for non-normally distributed data, and frequency and proportion for categorical data. All statistical inferences will be determined using two-sided tests. We will set a significance level of 0.05 and use 95% confidence intervals to measure the uncertainty of the estimate. Efficacy analyses will use last observation carried forward (LOCF) methodology to impute for cases not fully followed up during treatment. Pearson’s χ^2^ test will be used to compare the differences between the dropout rate and the dropout rate attributable to adverse events. Baseline data analyses (two sets) will include demographic indicators and general, primary, and secondary indicators before intervention. Measurement data will be compared using a paired *t*-test. For analyses of efficacy, for quantitative variables, comparisons between groups will be made by repeated measurement variance analysis and covariance analysis. For qualitative variables, comparisons between groups will be made using Pearson’s χ^2^ test, whereas central effects will be tested by a mixed-effects model. For rating variables, comparisons between groups will be made using the Kruskal-Wallis test. In terms of analyses of centre effects, the quantitative indicators will be tested by the general linear method, and the qualitative indicators will be tested by the Cochran-Mantel-Haenszel test methods. A logistic regression model will be used to evaluate and correct the rating variables.

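### The sample size is calculated for a one-sided t-test but all inference is to be two-sided, so the stated 80% power does not belong to the planned test (about 69% for a two-sided t-test at 21 per group)

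*Protocol article*

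**What the plan says.** The Sample size section of the protocol article gives these inputs: "Using a ratio of 1:1, α = 0.05, and 1 − β = 0.8", and continues "with a one-sided *t*-test, we calculated the appropriate trial sample size with 80% power". The effect is described only as "We defined efficacy as changes in at least one score with the visual analog scale (VAS"), which seems to mean a 1-point difference, although the wording is ambiguous. No SD is given. The result is that "a clinically significant difference could be detected using a sample of ≥21 patients in each group". On attrition it says "We increased this number to 30 per group to allow for a predicted dropout rate of 30"%.

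The Statistical analyses section states that "All statistical inferences will be determined using two-sided tests" and adds "We will set a significance level of 0.05 and use 95% confidence intervals". It makes no exception for the primary VAS comparison. No section declares a one-sided primary test or explains why the calculation and the analysis differ.

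**The concern.** At the same nominal 5%, a one-sided test has a lower critical value than a two-sided one. A sample just large enough for 80% power one-sided is therefore too small for 80% power two-sided. If the sample size text means what it says, the article credits the trial with a power that its own analysis rule does not deliver.

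Two things are at stake. A non-significant result would be read against a 20% risk of missing the target effect when the risk for the planned test may be higher. And a result with a one-sided p below 0.05 and a two-sided p above it could be argued either way, since the document contains support for both.

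**Working it through.** **Inputs.** From Sample size: α = 0.05 one-sided, power 0.80, 1:1 allocation, 21 evaluable per group, 30% dropout, 30 enrolled per group. From Statistical analyses: two-sided, 0.05. Not given: the SD of the VAS change.

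**Method.** Two-sample t-test with n per group, df = 2n − 2, noncentrality d·√(n/2), where d is the difference divided by the SD of change. Power is the probability that the noncentral t exceeds the critical value (in either tail for the two-sided test).

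**1. The plan's own figures.**
- Dropout step: 21 / (1 − 0.30) = 30 per group. This reproduces.
- The 21 itself cannot be fully reproduced without an SD. With a 1-point difference and a one-sided 5% test, 21 is the smallest adequate number when the SD is about 1.25 to 1.28. The figure is therefore possible but cannot be verified.

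**2. Effect implied by the text as written.** With n = 21 and df = 40, the one-sided critical value is 1.684. Power of 0.80 requires d·√(21/2) = 2.530, so d = 0.781. For a 1-point difference that is an SD of 1/0.781 = 1.28. If 21 was rounded up from just above 20, d could be as high as 0.801.

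**3. Same effect, two-sided test.** The critical value at df = 40 rises to 2.021.

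| Evaluable per group | Two-sided 5% power at d = 0.781 |
|---|---|
| 21 | 69.4% |
| 22 | 71.6% |
| 23 | 73.5% |
| 26 | 78.8% |
| 27 | 80.4% |
| 30 | 84.4% |

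Allowing for rounding (d = 0.801), power at 21 per group is 71.6%. The normal approximation gives 70.1% in place of 69.4%. None of this needs the SD: 21 per group, one-sided 5% and 80% together fix d, and so fix the loss.

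**4. What a two-sided 80% would need.** Either 27 evaluable per group (27/0.70 = 38.6, so 39 enrolled), or d = 0.886 with 21 per group, a difference about 13% larger (0.886/0.781 = 1.135).

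**5. Effect of baseline adjustment.** If the baseline and day-28 VAS have equal variances and correlation ρ, and the SD of change is held fixed, covariance analysis multiplies d by √[2(1 − ρ)/(1 − ρ²)]. The correlation is not in the document, so these values are assumed:

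| Assumed ρ | Factor | Effective d | Two-sided power, 21 per group |
|---|---|---|---|
| 0.3 | 1.240 | 0.968 | 86% |
| 0.5 | 1.155 | 0.901 | 81% |
| 0.7 | 1.085 | 0.847 | 76% |

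Power reaches 80% only for ρ up to about 0.55.

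**The case against.** **The 69% is not the power of the planned analysis.** Statistical analyses lists repeated-measures and covariance analysis for quantitative efficacy variables, not an unadjusted t-test. This stands. A reader might infer that the trial's true type II error is about 31%; the document does not support that as a flat statement. It holds for an unadjusted two-sided t-test with exactly 21 evaluable per group. Equally, the article's 80% was calculated for a t-test, and no correlation is given from which the gain could be worked out.

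**21 is a floor.** Thirty per group are to be enrolled, patients meeting the termination standards stay in the analysis, and LOCF is planned. Trial status reports 45 completers by the end of 2017; split evenly, that is 22 or 23 per group, or 72% to 74% power. This stands in part. The ceiling is about 84%, but the article itself predicts 30% dropout, its Follow-up section excludes patients who discontinue or deviate, and a carried-forward value does not carry the information of an observed one.

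**The word one-sided may be a slip.** A two-sided calculation also gives 80% at 21 per group with an SD of about 1.13 for a 1-point difference. If so, no power is lost. Without the SD a reader cannot tell, but one of the two sections still needs correcting.

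**The analysis is the stricter of the two.** True: if the two-sided rule is followed, type I error is not inflated. The fault lies in the stated power.

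**Conclusion.** The point holds. The two sections conflict on sidedness, and as written the 80% power does not apply to the two-sided test. Taking the calculation literally (d = 0.78), a two-sided t-test has about 69% power with 21 evaluable per group, at most about 72% allowing for rounding, and about 84% if all 30 contribute fully. These figures assume an unadjusted comparison of change scores; they do not depend on the missing SD.

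Two further inferences are tempting and unsupported. One is to try larger SDs, such as 1.5 or 2.0 for a 1-point difference, and report much lower power. Those values contradict the article's own calculation: one-sided power at 21 per group would then be only 68% and 48%, so most of the shortfall would come from the assumed SD and not from sidedness. The other is that baseline adjustment makes extra patients unnecessary. That rests on an assumed correlation, and at 0.7 power is 76%.

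**What to change.** - State one sidedness throughout. Keep the two-sided 5% test with 95% confidence intervals.
- Restate the sample size rationale on that basis, either as about 69% power for d = 0.78 or as 80% power for d = 0.89, both for a two-sided t-test with 21 evaluable per group. Add that power at d = 0.78 is about 84% if all 30 per group contribute fully.
- Give the VAS difference and the SD of change that were used. If the original calculation was in fact two-sided, these two numbers will show it, and only the word one-sided needs correcting.
- Consider naming the covariance analysis already listed, adjusted for baseline VAS, as the primary model. Present any gain in power as conditional on a stated correlation, not as a guarantee of 80%.

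The cost is wording only. The stated power becomes less favourable unless the calculation turns out to have been two-sided. The trial was still running when the article was written, so sidedness should be settled before the data are analysed.

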#### Recruitment, screening, and enrollment

Clinical recruitment staff will be in charge of enrolling the 60 participants sensitive to the allergens produced by *Artemisia* pollen. We will follow specific criteria to recruit, screen, enroll, and exclude participants. Patients will be enrolled if they meet all inclusion criteria, and will not be enrolled if they meet any of the exclusion criteria, rejection criteria, or termination standards. Participants will be briefed on the purpose, procedures, treatments, and possible risks of the trial. They will be clearly informed of their rights to discontinue participation in this clinical trial. After patients sign consent forms, researchers will assign them to the intervention groups. All of the personal privacy will be protected.

#### Inclusion and exclusion criteria

Inclusion criteria are confirmed AR and sensitivity to allergens from *Artemisia* pollen. Patients must be aged 18–65 years, provide written informed consent, volunteer to participate in this clinical trial, and complete the case report form and other records. Inclusion and exclusion criteria are detailed in Table 2.

**Table 2 Tab2:** Inclusion and exclusion criteria

Inclusion criteria	Exclusion criteria
Confirmed allergic rhinitis	Mental disorders
Sensitive to *Artemisia* pollen allergens	Systemic disease that the researchers consider to interfere with the study
Aged 18–65 years	Aged under 18 years or over 65 years
Provided informed consent and volunteered to participate in this clinical trial	Not cooperative during examination
Completed the case report form and other records	Employment changes leading to a possible loss to follow-up
	Dysgnosia or behavioral disorders
	The following conditions: nasal polyps, chronic sinusitis, severe nasal deviation, rhinitis medicamentosa, primary sleep disorders (> 1 night/week), obstructive sleep apnea, upper respiratory infection within 2 weeks prior to enrollment, or poorly controlled asthma
	Pregnant or may become pregnant, or lactating with a positive urine pregnancy test
	Drug abuse within the past 3 years
	Must sleep in different bed more than six times in 3 weeks or for more than 3 consecutive nights
	Smoked within the past 1 year
	Sensitive to indoor allergens such as dust mites and pet dander
	Other reasons, at the investigator’s discretion
	Refusal to continue the trial because of a poor curative effect
	Refusal to continue the trial for an unspecified reason
	Loss to follow-up because of a change of address or telephone number
	Loss to follow-up because of personal reasons

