### Trial status

This clinical trial was reviewed by the Ethics Committee of the First Hospital of Yulin in 2016. The first patient was enrolled in 2016. From the middle of 2016 to the end of 2017, 45 patients completed the treatment and observation periods. This clinical trial is expected to be completed at the end of 2018.

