## Discussion

The Atmosphere air purfier has been approved for daily use. The Atmosphere air purifier filter (101076CH) was certified to filter pollen allergens by Allergy UK. Before treatment commences, we will explain to patients in detail the research purpose, methods, and possible risks of the clinical trial, and also inform them explicitly of their right to discontinue their participation. Researchers will accept the research plan, treatment procedure, patients, research schedule, case report forms, and written informed consent forms. After the trial, if the participants are willing to continue treatment, we will provide appropriate therapies. Patients who suffer harm from participation in this clinical trial will be provided a certain amount of economic compensation or free treatment, especially if they suffer adverse events. Any moderate/serious adverse events will be reported to the Ethics Committee of the First Hospital of Yulin.

Reducing exposure to allergens can reduce the risk of conditions such as AR. We hypothesise that AR patients sensitive to the allergens produced by *Artemisia* pollen will not suffer symptoms in a pollen-free environment. AR patients can remove pollen from their homes using air purifiers, decreasing the risk of symptoms.

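### The entry rules do not tie the 28-day treatment to the Artemisia pollen season, so the effect may be diluted towards zero by an amount the article does not let us compute

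*Protocol article*

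**What the plan says.** The section on inclusion and exclusion criteria gives the core rule: "Inclusion criteria are confirmed AR and sensitivity to allergens from *Artemisia* pollen". It adds age limits, consent and completed records, and then says "Inclusion and exclusion criteria are detailed in Table 2". No row of Table 2 mentions the pollen season or current symptoms. One exclusion row reads "Sensitive to indoor allergens such as dust mites and pet dander", which leaves Artemisia pollen as the exposure the trial mainly relies on removing.

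The Design section says "All patients will accept a 4-week treatment period and a 4-week observation period" and attaches no calendar period to either. Table 1 schedules no pollen or allergen measurement.

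Trial status reports: "From the middle of 2016 to the end of 2017, 45 patients completed the treatment and observation periods". It continues: "This clinical trial is expected to be completed at the end of 2018". No recruitment months are named.

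The Discussion hypothesises that patients "sensitive to the allergens produced by *Artemisia* pollen will not suffer symptoms in a pollen-free environment", and cites a recommendation that purifiers be used in the ragweed season.

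**The concern.** The trial asks whether filtering Artemisia pollen out of the bedroom reduces symptoms. A patient treated when that pollen is absent gets the same exposure from an active filter as from a placebo filter, so on the Discussion's own hypothesis the filter should make little difference to that patient. Such patients add to the sample size and contribute little or nothing to the treatment effect.

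The stake is how a null result would be read. If an unknown share of patients had no target exposure, a small observed difference could mean an ineffective purifier or simply absent pollen. With no pollen measurement in Table 1, the scheduled data offer no direct way to tell these apart.

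**Working it through.** **Does any rule close the gap?**

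- Table 2: 5 inclusion and 17 exclusion rows, none on season.
- Recruitment, screening, and enrollment: patients enter if they meet all inclusion criteria and no exclusion, rejection or termination criterion. No season condition is added.
- Design: 4 weeks of treatment plus 4 weeks of observation, with no calendar anchor.
- Trial status: mid-2016 to the end of 2017 is about 18 months, so every calendar month occurs at least once in the reported span.

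Nothing written prevents off-season treatment. Nothing shows how often it happened either.

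**What does the sample size imply?** Inputs from the Sample size section: 1:1 allocation, one-sided α = 0.05, power 0.80, 21 per group, raised to 30 for 30% dropout. The target is "We defined efficacy as changes in at least one score with the visual analog scale (VAS"), read here as a 1-point difference between arms. The dropout step reproduces: 21/(1 − 0.30) = 30. The SD is not stated, so the 21 cannot be checked independently; it can only be solved for.

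- Normal approximation: SD = √(n/2)/(z₀.₉₅ + z₀.₈₀) = √10.5/(1.645 + 0.842) ≈ 1.30.
- Noncentral t: SD ≈ 1.28, that is, d = 1/1.28 ≈ 0.78.

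**Illustration of dilution.** Let e be the share of patients exposed to Artemisia pollen during treatment. Assume no effect in the rest and an unchanged SD. The mean effect becomes e × 1 point, and

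power ≈ Φ( e·√(n/2)/SD − 1.645 ).

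For e = 0.75, n = 21: 0.75 × √10.5/1.303 = 1.865; 1.865 − 1.645 = 0.220; Φ = 0.587.

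For e = 0.75, n = 30: 0.75 × √15/1.303 = 2.229; 2.229 − 1.645 = 0.584; Φ = 0.720.

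| Exposed share e | Mean effect (VAS points) | Power, 21 per arm | Power, 30 per arm |
|---|---|---|---|
| 100% | 1.00 | 80% | 91% |
| 90% | 0.90 | 72% | 85% |
| 75% | 0.75 | 59% | 72% |
| 50% | 0.50 | 34% | 44% |

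The noncentral t agrees to within half a percentage point in every cell.

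The Statistical analyses section specifies two-sided tests. With the same SD of 1.30 and 21 per arm, two-sided power is 70%, 46% and 24% at e = 100%, 75% and 50%. The step from 80% to 70% comes from the change of sidedness and is a separate matter; only the fall below 70% is dilution.

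**The case against.** The strongest objection is that the article does not show off-season treatment took place. A reader might infer from the 18-month span that enrolment ran all year, but 45 completers over that period fit seasonal waves of recruitment equally well. Patients also come by referral from their attending doctor to a hospital outpatient department, a route likely to favour those with symptoms. Both points stand. They limit the finding to what the rule permits; neither is itself a rule.

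A reader might also infer that off-season patients meet no pollen at all and start near zero on the VAS. The documents do not support this. Table 2 excludes sensitivity to indoor allergens, not to other pollens, so a co-sensitised patient may have symptoms, and particles to filter, outside the Artemisia season.

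A third tempting step is to call the lack of a minimum day-0 VAS an error, because a patient near zero cannot improve by a point. The primary outcome is a difference in VAS from baseline, compared between arms. A patient who enters early in the season with a low score is informative if the score rises less on the active filter. The Discussion's hypothesis is partly preventive in this sense. Enriching for baseline symptoms is a design choice, and its absence is not a fault.

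Patients entering late in the season may improve as pollen falls, but they do so in both arms. The concurrent control deals with that; what is lost is exposure, not validity.

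Finally, the power figures depend on an assumed exposed share, a back-solved SD and the assumption that the SD is unchanged. Scores near the floor would vary less, while mixing responders with non-responders adds variance. Because incomplete cases are to be carried forward by LOCF, the analysed number could approach 30 per arm, although the Follow-up section excludes those who discontinue or deviate. Hence both columns in the table.

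**Conclusion.** The point holds in limited form. As written, the criteria and design allow treatment outside the Artemisia season, and the reported accrual span includes every month. The randomised comparison stays fair; the consequence is dilution towards zero and a null result that would be hard to interpret.

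Its size is unknown. If 75% of patients were exposed, power would be about 59% at 21 per arm or 72% at 30, against 80% and 91% with full exposure. These figures assume d ≈ 0.78, a one-sided 5% test, zero effect in unexposed patients and an unchanged SD. If recruitment did cluster in season, the loss could be negligible.

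This is a moderate recommendation rather than a must-fix. Validity is intact, the loss cannot be quantified, and with 45 of 60 planned patients already through the trial, an entry change reaches at most 60 − 45 = 15.

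**What to change.** 1. **Remaining patients.** Add to Table 2 that the 28-day treatment must lie within the local Artemisia pollen season, with the calendar dates set in advance and stated.
2. **Patients already enrolled.** Before unblinding, use those same dates and each patient's day-0 date to define an in-season supportive analysis set. Report it beside the all-randomised result, which remains the main analysis. Membership depends only on calendar time, so the comparison between arms within the set stays fair.
3. **Day-0 VAS.** Use it as a covariate in both analyses rather than as an entry threshold. It is already a listed baseline variable, and covariance analysis is already planned.
4. **Reporting.** Give the number of patients entered by calendar month, so that readers can judge the exposed share.

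**Cost.** A short amendment and one extra pre-specified analysis, with no new patient measurements. Local season dates must be obtained, since the article gives none. The yearly recruitment window becomes narrower, which may delay the last patients, and the supportive set will be smaller and less precise than the full sample.
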